All groups 1, 2, 5, and 6 receive the full combined intervention (hypnosis + essential oil) in Phase 1, ensuring that Groups 5 and 6 have the same conditioning opportunity as their counterparts before the switch. Groups 3 and 4 allow us to isolate the effects of hypnosis itself (Group 3) and to account for any changes over time not attributable to the interventions (Group 4). Randomization is implemented via the SoSci Survey platform's built-in algorithm once participants are deemed eligible, ensuring allocation concealment. Because of the nature of the interventions, participants will know if they are using an oil or not (blinding is not feasible on the user level), but they will not be informed of the study hypotheses regarding which combination is expected to be most effective. The trial is single blinded in that the data analysts/statisticians will remain blind to group labels until after the primary analyses are completed, to prevent bias in outcome analysis.

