### Timeline and assessments

2.7

The study duration for each participant is 6 weeks from start to finish and 8 weeks in total for participants from groups 1, 2, 5, and 6, with three main measurement points: baseline (T0), post-Phase 1 (T1 at 6 weeks), and post-Phase 2 (T2 at 8 weeks). Additionally, brief self-reports are collected throughout the intervention period to track immediate effects and adherence.

**Week 0: Baseline (T0).** Upon enrollment and after screening, participants complete an online baseline questionnaire battery before any intervention. This includes demographic information, the Multidimensional Mood State Questionnaire (MDBF) (14), the GAD-7 (13), the Perceived Stress Scale (PSS-14) (15), the Pittsburgh Sleep Quality Index (PSQI) (16), the WHO-5 Well-Being Index (17), and the Penn State Worry Questionnaire (PSWQ, German short form) (18). These instruments establish baseline levels of relaxation, anxiety severity, perceived stress, sleep quality, psychological well-being, and trait worry, respectively. A subset of participants in Berlin also undergoes baseline physiological recording (continuous electrocardiogram (ECG) and pulse). The intervention commences on the day following completion of the baseline assessment.

**Weeks 1–6: Intervention Phase 1.** Participants follow the assigned intervention every two days (∼3 times per week). Before each session, they are prompted to rate their current subjective relaxation level using a simple Visual Analogue Scale (VAS) (e.g., “How relaxed do you feel right now?” on a 0–100 scale). Immediately after each session, whether hypnosis with or without essential oil, they rate their relaxation again on the VAS. These pre-post VAS measures for every session provide a running check of acute changes in relaxation per session and allow analysis of trends. During this phase, Groups 1, 2, 5, 6 use their essential oil aroma sticks during the hypnosis sessions as instructed, while Group 3 uses no essential oil (hypnosis only) and Group 4 simply continues with minimal intervention. The study platform tracks adherence.

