### Sample size calculation

2.11

The sample size was determined based on the primary outcome. The team conservatively anticipated a medium effect size for the group difference (Cohen's *f* ≈ 0.175, which corresponds roughly to d ∼0.35–0.40 in pairwise terms) given prior results based on the prior study on healthy individuals (11). Power analysis (*α* = 0.05 two-tailed, 1 − *β* = 0.80) for a one-way analysis of covariance (ANCOVA) with 4 groups and baseline as covariate, assuming the covariate explains ∼20% of variance, indicated needing about N ≈ 105 participants per group to detect *f* = 0.175. Allowing for up to ∼35% dropout, due to the fully online nature and 8-week duration, we decided to increase the target enrollment to ensure at least 105 completers per arm. Including the two extra groups for the conditioning test, the total planned sample size is *N* = 630 (105 × 6). This large sample will provide adequate power not only for primary comparison but also to explore secondary endpoints. Interim analyses are not planned; all data will be analyzed after study completion. The qualitative data from open-ended questions will be analyzed using deductive-inductive qualitative content analysis to identify patterns and themes in participants' experiences. We will integrate quantitative and qualitative findings in interpretation to understand the intervention's impact under consideration of multiple perspectives.

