### Data analysis

2.13

The primary outcome (MDBF calmness subscale change from T0 to T1) will be analyzed using an ANCOVA model. The model will include the study group (4 arms for primary analysis: Groups 1–4) as the independent variable and the baseline MDBF score as a covariate to control for any initial differences and improve statistical power. This aligns with the principle of analyzing covariance to account for baseline variance. The primary contrast of interest is whether either of the two combination groups (1: Hypnosis + Bergamot, 2: Hypnosis + Lavender) differ significantly from the control groups (3: Hypnosis-only, 4: Minimal intervention) in adjusted mean relaxation at T1. We anticipate a significant overall group effect; planned pairwise comparisons with appropriate correction for multiple comparisons, if needed, will examine specific differences, especially 1 vs. 3, 2 vs. 3, and combined 1&2 vs. combined 3&4. The primary hypothesis will be supported if Groups 1 and 2 show statistically greater increases in relaxation than Group 3 and Group 4 (*p* < .05, two-tailed).

For Phase 2 conditioning effects, a similar ANCOVA or mixed-model approach will be used at T2. The analysis will focus on the four groups that underwent Phase 2 aroma testing (Groups 1, 2 with match vs. Groups 5, 6 with mismatch). We will compare relaxation outcomes at T2 among these, using T1 values as covariates. A significant difference (e.g., match > mismatch) on the MDBF relaxation change from T1 to T2 or on the Phase 2 VAS responses would support H2.1. We may also use repeated measurements ANOVA or multilevel modeling incorporating all three time points (T0, T1, T2) to examine group × time interactions across the full study duration. The VAS data from each session will be analyzed using linear mixed-effects models, which can handle multiple observations per participant. These models will test differences in immediate relaxation gain per session by group and can also model time trends (session number as a predictor) to see if there is a significant upward trend in pre-session relaxation over the 6 weeks for each group (learning effect).

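### The Phase 2 match-versus-mismatch VAS test is not stated to use each participant's Phase 1 VAS responses, a valid pre-switch covariate that the trial already collects

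*Protocol article*

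**What the plan says.** The Data analysis section (2.13) of the protocol article restricts the Phase 2 comparison to the four aroma groups and names one covariate: "We will compare relaxation outcomes at T2 among these, using T1 values as covariates". It accepts a difference either on MDBF change from T1 to T2 or on the Phase 2 VAS responses as support for H2.1. It adds, as an option, repeated-measures or multilevel models using T0, T1 and T2.

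The session VAS data go into linear mixed models: "These models will test differences in immediate relaxation gain per session by group". Session number may be added as a predictor, and the only time trend described is over the six weeks of Phase 1.

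The Timeline and assessments section (2.7) says of the Phase 1 ratings: "These pre-post VAS measures for every session provide a running check of acute changes in relaxation per session and allow analysis of trends". The T1 survey listed there consists of MDBF calmness, GAD-7, PSS-14, PSQI, WHO-5, PSWQ and open questions, with no VAS. The Study groups section (2.6) explains that all four aroma groups receive the combined intervention in Phase 1, "ensuring that Groups 5 and 6 have the same conditioning opportunity as their counterparts before the switch".

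**The concern.** The phrase about T1 values provides a baseline for the MDBF route to H2.1 but none for the VAS route, because no VAS is taken in the T1 survey. As described, the VAS contrast therefore has no stated pre-switch adjustment. Yet every participant in it has already given a long run of before-and-after ratings on the same scale, under identical treatment within each pair (Groups 1 and 5, Groups 2 and 6).

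People differ in how large a change they tend to report on a VAS. If that stable difference stays in the between-person variance, the interval for match minus mismatch is wider than it need be. Groups 5 and 6 were added for this contrast, and no power figure is given for it. Both sides inhale a pleasant oil, and H2.1 allows a smaller rather than absent mismatch response, so the true difference may be modest. Section 2.13 justifies the baseline covariate in the primary ANCOVA partly by statistical power, and the same reasoning applies here.

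**Working it through.** **The plan's own figure.** The article states no sample size or power for the Phase 2 contrast. The only figure is for the primary outcome: "indicated needing about N ≈ 105 participants per group to detect *f* = 0.175", "assuming the covariate explains ∼20% of variance". A two-group comparison at d = 0.35 with residual variance 0.8 gives n = 2 × (1.960 + 0.842)² × 0.8 / 0.35² ≈ 103 per group, close to 105. The four-group ANCOVA as described gives 289 in total, about 73 per group. That discrepancy is a separate matter and does not affect this point.

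**Inputs from the article.** There are 105 per arm, so 2 × 105 = 210 per side. If 105 are randomised and 35% drop out, 105 × 0.65 = 68.25, about 68 per arm and 136 per side. Sessions every two days give 42 / 2 = 21 in Phase 1 and 14 / 2 = 7 in Phase 2.

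**Inputs assumed, because the article gives none.** The intraclass correlation (ICC) of session gains is taken as 0.1 to 0.5. The correlation between a person's underlying Phase 1 and Phase 2 gain is taken as g = 0.3 to 0.7.

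**Formulas.**
- Reliability of a mean over k sessions: k × ICC / (1 + (k − 1) × ICC).
- Share of variance in the Phase 2 mean gain explained by the Phase 1 mean gain: R² = (Phase 1 reliability) × (Phase 2 reliability) × g².
- Smallest difference detectable with 80% power, two-sided 5%, in SDs of the Phase 2 mean gain: 2.80 × √(1 − R²) × √(2/n).

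**Without the covariate.** 2.80 × √(2/210) = 0.273 SD, and 2.80 × √(2/136) = 0.340 SD.

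**With the covariate.** At ICC 0.1 the reliabilities are 2.1/3.0 = 0.700 and 0.7/1.6 = 0.4375, so at g = 0.3, R² = 0.700 × 0.4375 × 0.09 = 0.028. At ICC 0.5 they are 10.5/11 = 0.955 and 3.5/4 = 0.875, so at g = 0.7, R² = 0.955 × 0.875 × 0.49 = 0.409.

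| ICC | g | R² | Detectable, 210 per side | Detectable, 136 per side | Equivalent sample, 1/(1 − R²) |
|---|---|---|---|---|---|
| 0.1 | 0.3 | 0.028 | 0.270 | 0.335 | 1.03 |
| 0.1 | 0.7 | 0.150 | 0.252 | 0.313 | 1.18 |
| 0.3 | 0.5 | 0.169 | 0.249 | 0.310 | 1.20 |
| 0.5 | 0.3 | 0.075 | 0.263 | 0.327 | 1.08 |
| 0.5 | 0.7 | 0.409 | 0.210 | 0.261 | 1.69 |

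For illustration, power at a difference of 0.25 SD with 136 per side is 54.0% without the covariate and 55.2% to 76.5% with it. At three sessions a week (18 and 6 sessions) the extremes of R² are 0.667 × 0.400 × 0.09 = 0.024 and 0.947 × 0.857 × 0.49 = 0.398, so the range hardly moves.

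**T0 beside T1 for the MDBF.** Suppose the 20% assumed for the primary ANCOVA is carried over to T1–T2, so that r = √0.20 = 0.447, with the same value for T0–T1. Then R² from both = (r₁₂² + r₀₂² − 2 r₁₂ r₀₂ r₀₁) / (1 − r₀₁²).
- T0–T2 correlation 0.447: R² = 0.276, residual variance ratio 0.724/0.800 = 0.905.
- T0–T2 correlation 0.358: R² = 0.231, ratio 0.961.
- T0–T2 correlation 0.224: R² = 0.201, ratio 0.999.

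At 210 per side the detectable difference moves from 0.245 SD to between 0.233 and 0.244 SD.

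**The case against.** The strongest reply is that this is a secondary test in a condensed article. Covariate lists for such models are commonly left to an analysis plan, and the randomised contrast is unbiased without them. Two parts of that stand: the test is secondary, and no bias arises. The part about missing detail stands less well. The article does name the Phase 2 covariate and does make the Phase 2 VAS a route of its own to H2.1, and for that route the named covariate has no VAS counterpart.

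A reader might infer that the VAS model is limited to group and session number. The text does not go that far. Its predictor list is not closed, and one model across both phases is not excluded. The supportable statement is that the use of Phase 1 VAS in the Phase 2 contrast is not stated.

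A reader might also infer that T0 calmness is ignored. It is not: the same section offers an optional model with all three time points. That is no commitment, and with complete data an unconstrained group-by-time model gains nothing from T0 for the T1–T2 contrast. But the gain at stake is small anyway. Nor is the 20% a figure for T1–T2: the article gives it only for the baseline covariate of the primary ANCOVA. If T1–T2 were 0.60, T0–T2 0.36 and T0–T1 0.447, R² would rise only from 0.360 to 0.371.

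Finally, the Phase 1 gain is a response to audio plus oil, and the Phase 2 gain a response to scent alone. They may correlate weakly, and at the low end of the range the improvement is negligible. This limits the size of the benefit but does not affect the validity of the covariate.

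**Conclusion.** The point holds as a precision improvement to the Phase 2 VAS test of H2.1. Phase 1 VAS responses are collected from everyone in the contrast before match and mismatch diverge, and the plan does not state that they are used. The benefit runs from about 3% to about 41% of the variance of the contrast, equal to 1.03 to 1.69 times the sample. That range rests wholly on assumed correlations, and no single value within it can be defended from the article. Validity also assumes that participants do not learn of the oil switch during Phase 1, and the article does not say when they are told.

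Adding T0 to the Phase 2 MDBF ANCOVA is a minor optional extra worth about 0% to 10% of residual variance under the carried-over 20%. Neither change corrects a bias, and neither bears on the primary analysis.

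**What to change.** In section 2.13, or in the analysis plan before group labels are revealed, state that the Phase 2 VAS mixed model adjusts for two quantities per participant: the mean Phase 1 pre-to-post VAS gain and the mean Phase 1 pre-session level, each averaged over the sessions completed. A joint two-phase model would serve equally if it holds the Phase 1 means equal within each pair (Groups 1 and 5, Groups 2 and 6). State also when participants learn of the oil switch. If desired, add T0 beside T1 in the Phase 2 MDBF ANCOVA.

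The cost is a sentence or two of text, plus a rule for participants with few or no Phase 1 sessions. No new data, visits or participants are needed. Fixing the covariates in advance also removes the choice of adjusting after the results are seen.

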**Week 6: Post-Intervention Assessment (T1).** At the end of week 6, after the last Phase 1 session, all participants complete the T1 online survey. This repeats the same set of standardized questionnaires as at baseline (MDBF Calmness-Restlessness, GAD-7, PSS-14, PSQI, WHO-5, PSWQ) to quantify changes in relaxation and secondary outcomes from T0 to T1. In addition, participants are asked an open-ended question about their experience by asking for example, “Please describe how you experienced the intervention.” and “How did you integrate the intervention into your daily life?” This qualitative prompt allows them to reflect on any perceived benefits, challenges, or routine they developed over the six weeks. The responses, entered as free text, will later be analyzed to gain insights into engagement, acceptability, and subjective impact. This approach further allows for the identification of unforeseen themes that may emerge in connection with the intervention. Participants in the physiology subgroup come into the lab around this time for their second physiological measurement.

**Weeks 7–8: Conditioning Phase 2.** These two weeks focus on testing conditioned relaxation. Participants in Groups 1, 2, 5, 6 now use the aroma stick alone every two days, without using the hypnosis audio. Group 1 continues with bergamot essential oil inhalation; Group 2 with lavender oil, both maintaining the same CS as in conditioning (match). Group 5 switches to lavender oil only, after being conditioned with bergamot, and Group 6 switches to bergamot oil only, after conditioning with lavender. Group 3 and Group 4 will not be followed up in this phase. As in Phase 1, participants in the active arms (1, 2, 5, 6) will record a VAS relaxation rating before and after each aroma exposure to quantify any immediate relaxation effect from the scent. This data will show whether merely inhaling the familiar essential oil produces a significant calmness boost, and whether that holds true only for the matching scent or also occurs with a mismatched scent).

**Week 8: Final Assessment (T2).** At the end of week 8, all participants, including groups 3 and 4, complete a T2 survey which again includes the MDBF Calmness-Restlessness subscale and the secondary outcome questionnaires (GAD-7, PSS-14, PSQI, WHO-5, PSWQ). This final measurement captures any further changes after the Phase 2 period.

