### Hypotheses

2.10

**Primary Hypothesis (H1—Efficacy).** After six weeks of intervention (T1), participants receiving self-hypnosis combined with essential oil inhalation (Groups 1 and 2) will demonstrate greater improvement in subjective relaxation, as measured by the Multidimensional Mood Questionnaire (MDBF), compared to participants receiving self-hypnosis without essential oil (Group 3) or a minimal-intervention control (Group 4).

**Primary Null Hypothesis (H0).** There are no differences between intervention groups in change in subjective relaxation from baseline to T1. **Primary Alternative Hypothesis (H1).** At least one intervention group differs from the others with respect to change in subjective relaxation from baseline to T1.

**Secondary Hypothesis 2.1 (Conditioned Relaxation).** In Phase 2, the essential oil alone will elicit relaxation in those groups that have consistent pairing in Phase 1. Specifically, participants in the CS-match conditions (Group 1 with bergamot, Group 2 with lavender) will show a significant increase in relaxation as measured by pre-post VAS and possibly MDBF from T1 to T2, when exposed to the essential oil alone, whereas those in CS-mismatch conditions (Group 5 and 6, who receive a different oil than used in training) will have smaller or no relaxation response. We hypothesize a stimulus-specific conditioning effect, meaning the relaxation response is tied to the particular essential oil used during training, not just any pleasant essential oil.

**Secondary Hypothesis 2.2 (Broader Psychometric Benefits).** The combined hypnosis + essential oil intervention will lead to greater improvements in other psychological outcomes compared to hypnosis alone or minimal intervention. We expect to see reductions in self-reported anxiety symptoms (lower GAD-7 scores), perceived stress (lower PSS-14), and worry (lower PSWQ-d) as well as improvements in sleep quality (lower PSQI) and overall well-being (higher WHO-5) in Groups 1 and 2 vs. Groups 3 and 4 at T1. This hypothesis posits that beyond immediate relaxation, the 6-week intervention confers broader mental health benefits (less anxiety and stress, better sleep and mood), echoing findings that combined mind-body interventions can positively affect multiple domains of functioning.

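### Hypothesis 2.1 on conditioned relaxation can be supported by either of two endpoints without adjustment, and the sections disagree on which endpoint ranks first

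*Protocol article*

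**What the plan says.** Three sections of the Protocol article describe how hypothesis 2.1 will be judged.

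- **Data analysis (2.13)** gives the success rule. A significant difference between match and mismatch "on the MDBF relaxation change from T1 to T2 or on the Phase 2 VAS responses would support H2.1". Direction appears only as an example: "A significant difference (e.g., match > mismatch". The sentence gives no significance level.
- **Hypotheses (2.10)** expects the relaxation response "as measured by pre-post VAS and possibly MDBF from T1 to T2", so the VAS comes first and the MDBF is tentative.
- **Outcomes (2.9)** names MDBF calmness and the VAS ratings together as the main outcomes for Phase 2, with equal rank.

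On measurement, Timeline and assessments (2.7) says that Groups 1, 2, 5 and 6 "will record a VAS relaxation rating before and after each aroma exposure to quantify any immediate relaxation effect from the scent". The MDBF calmness subscale, which rates the current state, is part of the surveys at the end of week 6 (T1) and the end of week 8 (T2).

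The level of 0.05, two-tailed, is attached to the main hypothesis: "The primary hypothesis will be supported if Groups 1 and 2 show statistically greater increases in relaxation than Group 3 and Group 4". It appears again in Sample size calculation (2.11) for the primary analysis.

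**The concern.** The rule gives hypothesis 2.1 two routes to success and lets either one suffice. Neither multiplicity statement in the protocol reaches this pair. The correction to be used if needed in 2.13 belongs to the pairwise comparisons for the primary outcome. The later adjustment in the same section covers the anxiety, stress, sleep, well-being and worry scales in the four main groups. Hypothesis 2.1 uses neither those scales nor that set of groups.

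The two endpoints also differ in how directly they bear on the claim. The hypothesis describes relaxation on exposure to the oil alone, and the VAS is rated just before and just after each exposure. The MDBF change from T1 to T2 compares two end-of-phase surveys. As written, the MDBF alone could support stimulus-specific conditioning while the exposure ratings show nothing. Conditioning is one of the two things the trial sets out to evaluate, so its success rule should be settled before data are seen.

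**Working it through.** **The plan's own figure.** The protocol gives no error rate or power for hypothesis 2.1, so there is none to reproduce. The nearest figure is about 105 per group for the primary analysis, computed "for a one-way analysis of covariance (ANCOVA) with 4 groups and baseline as covariate" and "assuming the covariate explains ∼20% of variance". With f = 0.175, R² = 0.20, alpha 0.05 and power 0.80, take the noncentral F with λ = N f²/(1 − R²) on 3 and N − 5 degrees of freedom. This gives 73 per group (N = 292, λ = 292 × 0.030625/0.8 = 11.2), or 90 with R² = 0. The stated 105 is not reproduced. That is a separate matter and does not bear on this point.

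**Inputs for the error rate.**
- Two tests, either sufficient (2.13).
- Two-sided 0.05 for each test: an assumption, carried over from the primary hypothesis and 2.11.
- Correlation ρ between the two test statistics: not given, so shown from 0 to 0.9.

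**Formulas.** Let Z₁ and Z₂ be standard normal with correlation ρ under no match effect.
- Either direction counts: 1 − P(|Z₁| ≤ 1.96 and |Z₂| ≤ 1.96). At ρ = 0 this is 1 − 0.95² = 0.0975.
- Only match > mismatch counts: 1 − P(Z₁ ≤ 1.96 and Z₂ ≤ 1.96). At ρ = 0 this is 1 − 0.975² = 0.0494, against 0.025 for one test.
- Bonferroni, 0.025 two-sided for each test: at ρ = 0 this is 1 − 0.975² = 0.0494. Holm has the same rate when neither endpoint has an effect, because its first step is the Bonferroni step.

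| ρ | Either direction (ratio to 5%) | Match > mismatch only (ratio to 2.5%) | Bonferroni, either direction |
|---|---|---|---|
| 0 | 9.75% (1.95) | 4.94% (1.98) | 4.94% |
| 0.3 | 9.51% (1.90) | 4.76% (1.91) | 4.84% |
| 0.5 | 9.07% (1.81) | 4.54% (1.82) | 4.65% |
| 0.7 | 8.35% (1.67) | 4.17% (1.67) | 4.30% |
| 0.9 | 7.04% (1.41) | 3.52% (1.41) | 3.62% |

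**Power of the alternatives.** Match against mismatch is 2 × 105 = 210 per side. With 35% loss, 210 × 0.65 = 136.5, taken as 136. For illustration, assume a standardized difference of 0.35 and a plain two-group comparison with one value per person.

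| Per side | One test at 0.05 | One test at 0.025 |
|---|---|---|
| 210 | 0.948 | 0.911 |
| 136 | 0.823 | 0.740 |

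These figures describe a single endpoint at each level. They do not measure the power lost relative to the either-or rule, which would need effect sizes for both endpoints and their correlation.

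**The case against.** The strongest reply is that hypothesis 2.1 is secondary, that a difference is said only to support it, and that alpha handling among secondary hypotheses is often left to an analysis plan, which is not shown here. The first two parts stand and limit the weight of the point. The third does not remove it: the article states a success rule, and an analysis plan that followed it would inherit the defect.

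A second reply is that the hypothesis is directional. If only match > mismatch counts, false support stays below 5% in absolute terms. That is correct, but the relative inflation is about the same, and 2.13 gives the direction only as an example.

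Three stronger readings are tempting, and the document does not support them.
- *A reader might infer that the MDBF does not measure response to the scent at all.* The arms differ by random assignment of the Phase 2 oil, and each side of the contrast holds one bergamot and one lavender arm. A real T2 difference would therefore be caused by that assignment. The MDBF is less direct, not invalid. How the T2 rating is timed relative to the last inhalation is simply not stated.
- *A reader might infer that stopping hypnosis contaminates the T1 to T2 change.* Groups 1, 2, 5 and 6 all stop at the same point, and T1 is a covariate, so this effect is common to both sides of the contrast and cancels. It would matter only for a within-group reading.
- *A reader might infer that the protocol fixes 0.05 for each test.* It does not; that level is carried over from elsewhere.

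**Conclusion.** The point holds as a defect in a stated decision rule for a secondary hypothesis. The rule accepts either endpoint without adjustment, and 2.9, 2.10 and 2.13 rank the endpoints differently. Under an assumed two-sided 0.05 per test, the chance of false support is between 7.0% and 9.75% for correlations from 0.9 down to 0, or 1.4 to 1.95 times nominal. Near-doubling describes only low to moderate correlation, and both measures are self-rated relaxation in the same people. Counting only match > mismatch, the rate is at most about 4.9% against 2.5%. The primary efficacy conclusion is not affected.

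**What to change.** Reconcile 2.9, 2.10 and 2.13 so that all three name the same decisive test for hypothesis 2.1, and state its level and direction. The choice that best fits the wording of the hypothesis is the match (Groups 1 and 2) against mismatch (Groups 5 and 6) contrast in pre-to-post VAS gain over the Phase 2 sessions. It would come from the mixed model already planned, and support would be claimed only if match exceeds mismatch. T2 MDBF with T1 as covariate would then be reported as supportive.

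If both endpoints are to remain decisive, test them under Holm and say so.

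The change takes about one sentence, plus matching edits in 2.9 and 2.10. With a single decisive test, hypothesis 2.1 loses one unadjusted route to success but keeps the full level for the endpoint that remains. With Holm, both routes stay, but the smaller p-value must first pass 0.025. In the illustration above with 136 per side, that lowers the power of one endpoint from 0.823 to 0.740 at the first step.

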### Study groups

2.6

Participants are randomly assigned to one of six groups (arms) in a 1:1:1:1:1:1 ratio. Four groups are primary comparison arms for the main efficacy analysis at 6 weeks, and two additional groups are included for secondary analyses of conditioned stimulus specificity in Phase 2.

**Group 1: Hypnosis** + **Essential Oil (Bergamot).** Participants receive the self-hypnosis audio and inhale bergamot essential oil during each session in Phase 1. In Phase 2, they continue with bergamot oil only (no audio) on the same schedule. This is a conditioned stimulus (CS)-match condition where the same essential oil is used for conditioning and testing.

**Group 2: Hypnosis** + **Essential Oil (Lavender).** Participants receive the hypnosis audio plus lavender essential oil inhalation during Phase 1 sessions. In Phase 2, they use lavender oil only without hypnosis. This is the CS-match for lavender.

**Group 3: Hypnosis Only (No Oil).** Participants receive guided hypnosis sessions in Phase 1 with no aromatherapy. This controls for the effects of hypnosis alone. They do not use any aroma in Phase 2 either and effectively have no active intervention in weeks 7–8.

**Group 4: Minimal Intervention Control.** Participants do neither hypnosis nor essential oil in Phase 1. Instead, they may receive a minimal activity just to match time/expectation. This arm serves as a baseline and expectancy control. They also do not receive any aroma in Phase 2.

**Group 5: Hypnosis** + **Oil (Bergamot) → Switch to Lavender.** These participants start identical to Group 1 (hypnosis + bergamot oil in Phase 1). However, in Phase 2 they experience a CS-mismatch by switching to lavender without hypnosis. This group helps test if a different scent can trigger relaxation or if the effect is lost when the conditioned stimulus changes. It serves as a control for Group 1 in the conditioning analysis.

**Group 6: Hypnosis** + **Oil (Lavender) → Switch to Bergamot.** These participants mirror Group 2 initially (hypnosis + lavender in Phase 1), then switch to bergamot oil only in Phase 2, creating a CS-mismatch. This serves as a control for Group 2 to assess stimulus specificity.

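### The optional three-time-point analysis models T0 as an outcome, so its T0-to-T1 group × time component gives up precision that the plan's own ANCOVA keeps (minor)

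*Protocol article*

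**What the plan says.** Section 2.13 (Data analysis) specifies an ANCOVA for the primary outcome, the change in MDBF calmness from T0 to T1 in Groups 1–4. It includes "the baseline MDBF score as a covariate to control for any initial differences and improve statistical power". The secondary scales are also analysed by ANCOVA at T1 and T2 with baseline adjustment. The main Phase 2 comparison, Groups 1 and 2 against Groups 5 and 6, is made at T2 with the T1 value as covariate.

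The Phase 2 paragraph then adds an option: the team may also use repeated-measures ANOVA or "multilevel modeling incorporating all three time points (T0, T1, T2) to examine group × time interactions across the full study duration". It does not say that T0 enters as a covariate, or that the arms share a common T0 mean.

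Section 2.11 (Sample size calculation) gives the only information on the strength of the baseline score. The calculation was made "assuming the covariate explains ∼20% of variance". Section 2.6 (Study groups) confirms that "Participants are randomly assigned to one of six groups (arms) in a 1:1:1:1:1:1 ratio".

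**The concern.** The plan adjusts its primary model for baseline partly to gain power, then allows a second analysis of the same scale, covering the same interval, that gives part of that gain away. When T0 is an outcome and each arm has its own T0 mean, the T0-to-T1 interaction compares raw changes. It subtracts the whole baseline score, where ANCOVA subtracts only the fraction that predicts T1. Because the arms are randomised, they share one expected T0 mean, and estimating six separate ones only adds noise.

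At stake is a supplementary result on the primary scale that is predictably weaker than the ANCOVA and can differ from it through chance imbalance at T0. Repeated-measures ANOVA, the first method named, has this form in its conventional use. A multilevel model has it unless the T0 means are constrained.

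**Working it through.** **Inputs.** From section 2.11: baseline R² about 0.20, f = 0.175, d about 0.35–0.40, two-sided α = 0.05, power 80%, 105 per group. From section 2.6: equal allocation. Assumed, because the article does not give them: equal SDs at T0 and T1 (relaxed in step 3) and complete data.

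**1. The plan's own figure.** With the noncentral F and λ = N f²/(1 − R²), the four-group ANCOVA as described needs 73 per group for 80% power. A two-group contrast with the same f and R² needs 104. The stated 105 is therefore reproduced only on a pairwise reading, and that reading uses the 20%. This is a separate matter. The variance ratios below do not depend on it.

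**2. Variance of the T0-to-T1 group contrast, relative to T1 alone.** r = √0.20 = 0.447.

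- T1 alone: 1.000
- ANCOVA: 1 − r² = 0.800
- Change score: 2(1 − r) = 1.106

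The ratio of change score to ANCOVA is 2(1 − r)/(1 − r²) = 2/(1 + r):

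| R² | r | Change | ANCOVA | Change/ANCOVA |
|---|---|---|---|---|
| 0.20 | 0.447 | 1.106 | 0.80 | 1.38 |
| 0.25 | 0.500 | 1.000 | 0.75 | 1.33 |
| 0.30 | 0.548 | 0.905 | 0.70 | 1.29 |

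At R² = 0.20, 105/1.382 = 76 per arm.

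**3. Unequal SDs.** The change-score variance is SD0² + SD1² − 2r·SD0·SD1, and the ANCOVA variance is SD1²(1 − r²). The difference is (SD0 − r·SD1)², which is never negative. The direction of the loss against ANCOVA therefore needs no assumption about r or the SD ratio.

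**4. Checks.** In 4,000 simulated two-arm trials at 105 per arm, the relative variances were 1.10 (change), 1.00 (T1 alone) and 0.80 (ANCOVA). In one simulated data set, the interaction from a mixed model with free T0 means equalled the difference in mean change to rounding (0.025 for both). Holding the T0 means equal in that data set lowered the standard error from 0.148 to 0.128.

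**5. Power for the T0-to-T1 comparison at R² = 0.20, equal SDs.**

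| | ANCOVA | T1 alone | Change |
|---|---|---|---|
| Four arms, f = 0.175, 105 per arm | 93.3% | 86.3% | 82.4% |
| Four arms, f = 0.175, 68 per arm (35% loss) | 77.3% | 66.7% | 61.8% |
| Two arms, d = 0.35, 105 per arm | 80.6% | 71.4% | 67.0% |

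**6. Joint four-arm test over T1 and T2 (6 df).** Assume all three correlations are 0.447 and an effect of f = 0.175 that persists to T2. Power is 86% with free T0 means and 98% with T0 as covariate. If half the effect persists at T2, it is 72% and 89%.

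**7. Chance imbalance.** One standard error of the T0 difference is √(2/105) = 0.138 SD. The change score and ANCOVA then differ by (1 − 0.447) × 0.138 = 0.076 SD, about 22% of d = 0.35.

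**8. T1-to-T2 contrast.** The relevant correlation is r(T1,T2), which is not given. Over an assumed range of 0.3 to 0.8, change-score variance runs from 1.40 to 0.40 times T2 alone, and ANCOVA from 0.91 to 0.36. The ratio runs from 1.54 down to 1.11, so the 1.38 cannot be transferred.

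**The case against.** The strongest reply is that nothing decisive rests on this sentence. The analysis is one the team may use. The primary hypothesis is judged on the ANCOVA, and the main Phase 2 comparison already adjusts for T1. All of this stands, and it keeps the point minor.

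Second, the multilevel wording does not exclude a common T0 mean, so one of the two permitted options already has room for the remedy. This also stands. The loss applies to repeated-measures ANOVA and to a multilevel model with arm-specific T0 means, not to every model the sentence allows. The point is still more than unstated detail, because the first-named method, used in the ordinary way, gives the less precise result.

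Third, the sentence sits in the Phase 2 paragraph, where the match/mismatch contrast runs from T1 to T2. Groups 5 and 6 have the same Phase 1 treatment as Groups 1 and 2, so no T0-to-T1 difference is expected between matched and mismatched arms. That is correct, and it limits the figures to the T0-to-T1 component and, under the stated correlations, the joint test.

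Fourth, the change-score contrast is unbiased under randomisation, and at 105 per arm its four-arm power (82.4%) still exceeds the 80% target. Two valid analyses will sometimes disagree on significance: about 18% of simulated two-arm comparisons at d = 0.35 did. The issue is efficiency, not validity.

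A reader might go further and infer that the three-time-point model is worse than ignoring baseline altogether. The documents do not support this. The margin is 1.106 against 1.000, about 5% in the standard error. It vanishes at R² = 0.25 and reverses at 0.30 (0.905). It also reverses at R² = 0.20 if the T0 SD is below 0.894 times the T1 SD. The article gives R² only approximately and no SDs.

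**Conclusion.** The point holds as a minor efficiency improvement. If the optional analysis is run as repeated-measures ANOVA, or as a multilevel model with arm-specific T0 means, its T0-to-T1 group × time component is a raw change-score contrast. That contrast cannot be more precise than the ANCOVA used elsewhere in the plan, ignoring the negligible cost of estimating one slope. The direction holds for any correlation and SD ratio. The size, 1.38 times the variance at R² = 0.20 and 1.29 at 0.30, assumes equal SDs and complete data and takes the plan's R² as the squared T0–T1 correlation. The primary T1 result and the main Phase 2 result are not at risk.

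**What to change.** If this analysis is kept, remove the repeated-measures ANOVA option and replace the sentence with wording such as: *As an analysis supplementary to the ANCOVA, a linear mixed model will take T1 and T2 as outcomes, with group, time, group × time, T0 and T0 × time as fixed effects; group differences at T1 and at T2 will be reported.* An acceptable alternative is to model all three time points with the T0 mean held equal across the randomised arms.

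The main match/mismatch analysis with T1 as covariate should stay as it is. The group × time term in the revised model is still a T1-to-T2 change contrast, adjusted only for T0, so it does not replace that analysis.

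The cost is one sentence. The T0 score is already collected, no further data are needed, and both forms are valid under randomisation.
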